### Recruitment

The researcher at the intervention site and the clinical trials nurses at the control site will review the clinical record of newly admitted patients and undertake necessary screening for eligibility, and if required, speak with the clinical staff to clarify any aspects of inclusion criteria such as cognitive status. This visit will not directly involve the patient. During the course of the study at the intervention site, the researcher will maintain a visible presence at the facility to ensure that all eligible patients are identified and recruited in a timely manner. The involvement of experienced clinical trials nurses at the control site is expected to enhance participant recruitment to the study at this facility.

### Data collection methods for the intervention arm of the study

The patient and family participant timeline and data collection for both arms of the study are summarised in Table 1, and a detailed description of these key tasks for the intervention arm is outlined below.

**Table 1 Tab1:**
[figure not shown]
VOICE Study patient and family participant timeline for enrolment, interventions, and assessments at intervention and control sites

*Day 1* day of admission, *CS* control site, *IS* intervention site, *NCCN DT* National Cancer Collaborative Network Distress Thermometer, *PHQ-4* Patient Health Question Questionnaire-4

#### Days 1–2 screening

Recruitment of patients and family members will commence Days 1–2 following admission. The researcher will review the clinical record of all newly admitted patients to screen for eligibility according to the inclusion criteria for the VOICE Study. Clinical staff will clarify any issues or information concerning the patient’s status such as their cognitive status or palliative care phase [24] .

#### Days 2–3 recruitment and consent

On Days 2–3 of admission, all eligible patients will receive a formal written “Invitation to attend a Patient-Centred Family Meeting” and if they are interested, the patient will be given the Patient-Centred Family Meeting Introductory Patient Information sheet. The study will be discussed with the patient and issues addressed by the researcher. Interested patients will be provided with the Patient-Centred Family Meeting Participant (patient) Information Statement and Consent Form. Patients who agree to participate will be asked to complete the consent form. If the patient requires more time to consider participation, the researcher will return at a later date to finalise recruitment.

#### Days 3–5 baseline data collection

Consented patients will then be asked to complete the Patient-Centred Family Meeting Patient Information Booklet that includes:(i)baseline patient information, demographics and questions that will guide the Patient-Centred Family Meeting agenda,(ii)the QUAL-EC questionnaire [18, 32](iii)the NCCN Distress Thermometer [20](iv)the single question measure: “To what extent are you at peace?”.

Consented patients will be asked to nominate and provide contact details of the primary support person who the patient would like to participate in the proposed Patient-Centred Family Meeting. If required, the researcher or social worker will assist with contacting the support person and teleconferencing will be made available if required. The patient may also nominate additional family members or significant others to be included in the study and/or attend the Patient-Centred Family Meeting.

The nominated family member(s) will be contacted and given a copy of the Patient-Centred Family Meeting introductory Family Information. The study will be explained to the family member(s) and questions or issues discussed. A Patient-Centred Family Meeting Participant (family) Information Statement and Consent Form will be provided and further questions addressed. Interested family member(s) who are on site will be consented immediately or the consent form will be completed prior to the Patient-Centred Family Meeting commencing. The Patient-Centred Family Meeting Family Information Booklet which includes questions about the patient and pre-meeting measures: QUAL-E (Family) questionnaire; the NCCN Distress Thermometer; and the PHQ-4 will be completed prior to the meeting.

If an invited family member(s) or significant other(s) do not meet the criteria or will not consent, the patient will nominate an alternative participant. If this is not possible, the patient will be excluded.

#### Days 5–10 Patient-Centred Family Meeting and repeat patient measures

The researcher or social worker will arrange the Patient-Centred Family Meeting in consultation with the patient, family, and clinicians between days 5–10. During the Patient-Centred Family Meeting, the researcher will complete the family meeting observation sheet. Within 24–48 h post-meeting, the researcher will interview the patient using the Patient-Centred Family Meeting patient semi-structured interview schedule. The patient will also complete repeat QUAL-EC and NCCN Distress Thermometer measures.

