### Research design

The VOICE Study Research Protocol (Version 5.6, 11.3.2017) will utilise a mixed methods quasi-experimental (pre-post-test) design. The specific strategy used to mitigate factors that may compromise internal validity will be a non-equivalent control group design. This design incorporates a comparison (control) group and collection of equivalent pre-test and post-test measures for the intervention and comparison (control) groups [28]. The SPIRIT checklist [29] was used to inform the study protocol and is included as an additional file.

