### Sample size

Twenty inpatients will be recruited from each facility. At each site, the patient will nominate one family member (or equivalent) as the primary support person to participate in the study. A total of 20 patient-family dyads will be recruited for each site, resulting in 40 participants at each site and a total of 80 participants for the entire study. The total number may exceed this if additional family participants wish to attend the Patient-Centred Family Meeting or standard care family meeting. Data will be collected from additional family participants who consent to study inclusion. A power calculation was not undertaken as this will be a feasibility study.

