#### Day 7 repeat patient measures

On Day 7, the patient will complete repeat measures of the QUAL-EC questionnaire and the NCCN Distress Thermometer. The researcher will interview the patient using the family meeting patient semi-structured interview schedule if a family meeting has been held. If the patient participates in a family meeting after Day 7, the researcher will undertake the interview at a convenient time for the patient.

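### An intervention-site patient who stays enrolled but has no meeting has no scheduled QUAL-EC or Distress Thermometer post-test, whereas the control-site post-test falls due on Day 7 with or without a meeting

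*Protocol article*

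**What the plan says.** **Intervention site** (Protocol article, *Days 5–10 Patient-Centred Family Meeting and repeat patient measures*). The meeting is arranged "in consultation with the patient, family, and clinicians between days 5–10". The next patient contact follows it: "Within 24–48 h post-meeting, the researcher will interview the patient using the Patient-Centred Family Meeting patient semi-structured interview schedule". The scales come directly after that: "The patient will also complete repeat QUAL-EC and NCCN Distress Thermometer measures". The text gives no calendar day for them and no rule for a patient whose meeting does not take place. *Quantitative measures* uses the same anchor, describing the Distress Thermometer as a before-and-after-meeting measure.

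**Control site** (*Day 7 repeat patient measures*). "On Day 7, the patient will complete repeat measures of the QUAL-EC questionnaire and the NCCN Distress Thermometer". In that section only the interview depends on a meeting having been held.

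**Design and analysis.** *Research design* relies on "collection of equivalent pre-test and post-test measures for the intervention and comparison (control) groups" to protect internal validity. *Statistical methods, Quantitative data* plans between-group comparisons of the scales. *Statistical methods, Qualitative data* uses the percentage of completed questionnaires to judge whether the measures are feasible and suitable, without giving a denominator.

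**Size.** "Twenty inpatients will be recruited from each facility". There is no power calculation: "A power calculation was not undertaken as this will be a feasibility study".

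**The concern.** The issue is who is measured, not on which day or with which interview. If the protocol is followed literally, patient follow-up data at the intervention site come from those who had a meeting, and at the control site from everyone still in the study and able to answer on Day 7.

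Missed meetings are plausible. The inclusion criteria admit patients in the Unstable and Deteriorating phases, with a performance score as low as 30 and an expected survival that may be only 14 days. A meeting also needs patient, family and clinicians together within a few days. A patient may decline it, become too frail for it, or not be scheduled in time, and still be able to complete two short scales.

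Two results are exposed:

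- **The between-site comparison of QUAL-EC and the Distress Thermometer.** If patients without a meeting tend to be sicker or more distressed, their absence improves the intervention group's follow-up scores.
- **The completion percentage.** This bears on primary objective (iii), the suitability and feasibility of the measures, and so on the choice of outcomes for the later randomised trial.

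**Working it through.** **1. The plan's own figure.** 20 dyads × 2 people = 40 per site, and 40 × 2 sites = 80, which agrees with "resulting in 40 participants at each site and a total of 80 participants for the entire study". The patient comparison is therefore 20 against 20 at most. Alpha, power, effect size and SD are not stated, so there is no power figure to reproduce.

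**2. When each post-test falls due.**

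| | Intervention site | Control site |
|---|---|---|
| Patient scales | With the contact 24–48 h after a Day 5–10 meeting: Day 5 + 1 = 6 to Day 10 + 2 = 12 | Day 7 |
| Enrolled, no meeting | No occasion given | Still Day 7 |
| Family scales | Day 14 | Day 14 |

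The family scales do not depend on a meeting at either site, so the asymmetry concerns the patient scales only.

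**3. Illustrative size of the selection.** Let m of the 20 intervention patients have no meeting, f = m/20, and let d be the gap in mean score (in SD) between those who met and those who did not, with those who met doing better. Then:

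- mean of those who met − mean of all consented = f × d
- standard error of the site difference = √(1/(20 − m) + 1/20), in SD units
- rejection rate with no true effect = chance that a two-sided 5% normal test rejects when the difference is shifted by f × d

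The protocol gives neither f nor d. The assumed ranges are f = 10–30% and d = 0.5–1.0 SD.

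| m (f) | Bias, d = 0.5 | Bias, d = 1.0 | SE | Rejection rate, no true effect |
|---|---|---|---|---|
| 2 (10%) | 0.05 SD | 0.10 SD | 0.325 | 5.3–6.1% |
| 4 (20%) | 0.10 SD | 0.20 SD | 0.335 | 6.0–9.2% |
| 6 (30%) | 0.15 SD | 0.30 SD | 0.348 | 7.1–13.8% |

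**4. Why these are upper figures.** They treat every patient without a meeting as someone who could have answered. If only k of the m could, the bias that a scheduled post-test would remove is k × d/(20 − m + k). This equals f × d when k = m and is zero when k = 0.

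**5. Completion percentage.** With 2 to 6 patients never due a post-test, 18 to 14 remain. If all of these complete, completion is 100% of those due, but 18/20 = 90% down to 14/20 = 70% of those consented.

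**The case against.** The strongest case against is that this reads a gap in a condensed article as a rule. Table 1, which carries the timeline for both sites, was not available for this check, and the article refers to a full protocol that is not shown. The 24–48 h clause grammatically governs the interview, and the sentence on the scales states no condition. The subsection heading could be taken as a Day 5–10 calendar window for the measures.

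Part of this stands: Table 1 or the full protocol may hold a fallback. However, the article sets out both schedules in detail, and they differ in who is measured. A contact after a Day 10 meeting falls on Days 11–12, so the heading does not work as a literal measurement window. The before-and-after-meeting wording elsewhere supports the meeting-linked reading.

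Three stronger readings are tempting, and the protocol does not support them:

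- **That follow-up is complete at the control site and selective only at the intervention site.** Control patients who die, deteriorate, become cognitively impaired or withdraw before Day 7 are lost too. Someone too unwell to meet may also be too unwell for the scales at either site. Nor is cognitive impairment the only exit: patients are excluded if no family member consents, and withdrawal is foreseen generally. The missing rule matters only for those who stay enrolled without a meeting, possibly a small group.
- **That a bias favouring the intervention is established.** Meetings missed because of family availability or scheduling need not involve sicker patients. Even the largest illustrative bias, 0.30 SD, is below its standard error of 0.348 SD.
- **That the completion percentage is inflated.** No denominator is stated, and the protocol requires incomplete data and the reasons to be documented, which could expose the gap.

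It is also fair that the sites are not randomised, the study is unpowered, and the primary outcome is qualitative. These limit the consequence but do not justify an avoidable extra selection.

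**Conclusion.** The point holds as an asymmetry in the written schedule. The patient post-test follows the meeting at one site and the calendar at the other, and no visible text gives a post-test to an enrolled intervention patient without a meeting. This sits badly with the reliance on equivalent post-test measures.

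The consequence is possible rather than demonstrated. Under the assumed 10–30% without a meeting and a 0.5–1.0 SD gap, the bias is at most about 0.05–0.30 SD. It would probably favour the intervention if missed meetings track worse health, and would be smaller if they are logistical or if those patients could not have answered. Completion is overstated only if post-tests that fell due are the denominator. The conclusion also assumes that Table 1 and the full protocol contain no fallback. It is worth correcting because the remedy is cheap and the results are meant to inform a phase III trial. It does not undermine the qualitative assessment of feasibility and acceptability.

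**What to change.** In the intervention-site Days 5–10 section, state that patients still enrolled and able, with no meeting by the end of the Day 5–10 window, are offered the repeat QUAL-EC and Distress Thermometer at the close of that window. Then:

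- keep these patients in the intervention group for the between-site comparison;
- use all consented patients as the denominator for completion at both sites;
- report how many intervention patients had no meeting, and why;
- add a second summary restricted to patients who had a meeting.

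Closing the window at Day 10 is later than the control site's Day 7, but lies within the Day 6–12 range that meeting recipients already have. A common fixed day for all patients at both sites would also remove the timing difference, but would detach the intervention post-test from the meeting.

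The cost is one protocol sentence and a few extra short questionnaires for frail patients, given by a researcher already on site. The intervention mean may look less favourable as a result.

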#### Day 14 repeat family measures

On Day 14, family participant(s) will complete the Patient-Centred Family Meeting family feedback questionnaire and repeat measures of the QUAL-E (Family), NCCN Distress Thermometer and PHQ-4 by telephone or on-site according to their availability. A sample of family members (*n* = 10) will also participate in an interview, using the QUAL-E (Family) questions as prompts for further discussion about families’ views concerning the relevance of the measures, time taken to complete, any issues about the measures and their preference(s) for a particular measure. This interview will be conducted by telephone or face-to-face based on availability.

### Data collection for the intervention arm of the study for clinicians

After the completion of a number of Patient-Centred Family Meetings, a focus group will be convened to seek the views of multidisciplinary team members who have cared for the patients recruited to the VOICE Study and attended at least one Patient-Centred Family Meeting. Additional focus groups will occur during the course of the VOICE Study to include additional team members and ensure data saturation. However, each team member will only be required to attend one focus group.

### Data collection methods for the control arm of the research study (Table 1)

#### Days 1–2 screening

A clinical trials nurse will undertake the same eligibility screening procedures as undertaken at the intervention site.

#### Days 2–3 recruitment and consent

On Days 2–3 of admission, eligible patients will receive the introductory patient information and the study will be discussed with the patient and any questions or concerns addressed. Interested patients will receive the Participant (patient) Information Statement and Consent Form and written consent will be obtained. If the patient requires more time to consider, the clinical trials nurse will return to finalise recruitment.

#### Days 3–5 baseline data collection

The consented patient will complete the Patient Information Booklet that includes information about family, the QUAL-EC and the NCCN Distress Thermometer. Consented patients will nominate a primary support person to participate in the study. The patient may also invite additional family members or significant others to be included in the study and/or attend any family meeting held. The nominated family member(s) will be given study information and any questions or issues discussed. Consented family member(s) will complete the Family Information Booklet that includes patient-related questions and the outcome measures used at the intervention site. If the family member is unavailable, the family member will be requested to complete the consent form and Family Information Booklet by Day 7 of the patient’s admission. If the nominated family member(s) does not meet the criteria or will not consent, the patient will nominate an alternative person. If this is not possible, the patient will be excluded.

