### Intervention

The intervention is a planned face-to-face Patient-Centred Family Meeting for the inpatient and family member(s) after inpatient admission to a specialist palliative care facility that is the designated intervention site. The duration of the Meeting will be 60 min, although this may vary depending on patient and family members’ needs. The intervention is designed to be “patient-centred” with the patient setting the agenda in advance so that their concerns and issues are addressed. The baseline information about the patient's issues, concerns and expectations of their inpatient stay will inform the Patient-Centred Family Meeting agenda. Meeting discussion may include clinical and psycho-social issues, preparation for death and other key areas of importance for that patient and family. The Meeting will be scheduled as soon as practicable after the patient’s admission and be conducted in a private space with members of the palliative care multidisciplinary team. Routinely, the palliative care consultant and/or registrar and social worker will attend. Other members of the team will participate as required or as requested by the patient during preparation for the meeting. A participant attendance sheet will be completed.

The palliative care consultant or social worker will facilitate the meeting, according to the Manual for Patient-Centred Family Meetings. The researcher will provide education to the clinical staff prior to commencement of the study and will attend Patient-Centred Family Meetings to observe for fidelity to the Manual procedures.

Other than the Patient-Centred Family Meeting, all other usual palliative care practices will be provided to the patient and their family.

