### Control

The Patient-Centred Family Meeting will not be offered at the control site. Usual care will be maintained which may include a family meeting that is held as part of the facility’s usual care. The need for a family meeting will be determined as per the facility’s usual clinical practice. A proportion of these “standard” family meetings will be observed using the family meeting observation sheet.

For both the intervention and control sites, if, following consent, the patient’s mental state changes, the researcher or clinical trials nurse will consult the clinical team concerning the appropriateness of the patient continuing in the study. The clinical team will be asked to consider the patient’s mental state to assess if the patient fulfils the exclusion criteria of cognitive impairment. If the patient does fulfil the exclusion criteria, the patient will be withdrawn from the study. The family member(s) participating in the study will be informed and the family member will also be withdrawn from the study.

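### The control-site pre-test is fixed by admission day only, so it can follow a usual-care family meeting, whereas the intervention-site pre-test must precede the planned meeting

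*Protocol article*

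**What the plan says.** Under Research design, the protocol article relies on a non-equivalent control group to protect internal validity, including "collection of equivalent pre-test and post-test measures for the intervention and comparison (control) groups".

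For the intervention arm, the section on Days 3–5 baseline data collection puts the patient measures in the booklet that also holds the agenda questions, and says the family booklet "will be completed prior to the meeting". The meeting itself is arranged for Days 5–10.

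For the control arm, the section of the same name says: "The consented patient will complete the Patient Information Booklet that includes information about family, the QUAL-EC and the NCCN Distress Thermometer". Consented relatives complete their booklet in the same window. If a relative is not available, "the family member will be requested to complete the consent form and Family Information Booklet by Day 7". Neither instruction refers to a family meeting.

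On meetings at the control site, the Control section says "Usual care will be maintained which may include a family meeting", and "The need for a family meeting will be determined as per the facility’s usual clinical practice". The section on Day 7 repeat patient measures provides both for a meeting already held by Day 7 and for one held later.

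At the intervention site, usual care continues alongside the study meeting: "Other than the Patient-Centred Family Meeting, all other usual palliative care practices will be provided to the patient and their family". The eligibility criteria do not mention a family meeting earlier in the admission at either site.

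**The concern.** The two sites anchor the pre-test differently. At one it is defined relative to the planned meeting, at the other relative to the day of admission. A control score labelled pre-test can therefore be a score taken after a family meeting. In such a dyad, whatever lasting benefit or burden the meeting brought is already in the baseline and drops out of the change from baseline.

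The family route is the more exposed. A relative who could not be reached on Days 3–5 might first come to the unit for a standard meeting and fill in the booklet afterwards. The intervention schedule blocks that order for the planned meeting. The control schedule has no matching line.

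What is at stake is the reading of the quantitative pre-post data and the planned comparison of the groups on the Distress Thermometer, PHQ-4, QUAL-EC and QUAL-E (Family), and the use of those results in planning the phase III trial. The qualitative primary outcome is not touched.

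**Working it through.** **The plan's own figure.** Sample size gives 20 dyads per site at two sites: 20 × 2 = 40 participants per site, and 40 × 2 = 80 in total. This agrees with the stated 80. No power calculation, effect size, standard deviation or meeting rate is given.

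**Timing, side by side.**

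| | Intervention site | Control site |
|---|---|---|
| Patient baseline | Days 3–5; feeds the meeting agenda | Days 3–5; no link to a meeting |
| Family baseline | Before the planned meeting | Days 3–5, or by Day 7 if unavailable |
| Planned study meeting | Days 5–10 | None |
| Usual-care meeting | Not ruled out, any day | Any day, by local practice |
| Patient repeat measures | 24–48 hours after the study meeting | Day 7 |
| Family repeat measures | Day 14 | Day 14 |
| Criterion on an earlier meeting | None | None |

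Three things follow.

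1. At the control site, a meeting on Days 1–5 can precede the patient baseline, and one on Days 1–7 can precede the family baseline. Neither order is a deviation.
2. At the intervention site, the planned meeting cannot precede baseline if the protocol is followed. A usual-care meeting can.
3. A control meeting can also fall after the patient's Day 7 repeat measures. In that case only the interview moves, so the meeting date is needed relative to the repeat measure as well as the baseline.

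**Size, on assumed values only.** Suppose *k* of 20 control dyads give baseline after a meeting that shifts a score by *d* SD, and that the shift persists to the repeat measure. Each such dyad's change then omits *d*, so the control mean change is off by (*k*/20) × *d*:

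| *k* of 20 | *d* = 0.2 | *d* = 0.5 | *d* = 0.8 |
|---|---|---|---|
| 1 | 0.01 | 0.025 | 0.04 |
| 2 | 0.02 | 0.05 | 0.08 |
| 5 | 0.05 | 0.125 | 0.20 |
| 10 | 0.10 | 0.25 | 0.40 |

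Both *k* and *d* are assumptions. The table shows how the error scales and does not estimate it for this study.

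**The case against.** The strongest reply is that the comparator is usual care, not a standard meeting. Many control dyads may never have a meeting, so baseline cannot be defined by one, and an early meeting is part of the control condition. Anchoring to admission is then a natural choice, and patient baseline falls on Days 3–5 at both sites. Equivalent measures may also mean no more than the same instruments. This stands as a defence of an admission-day baseline. It does not make a score taken after a meeting equivalent to one taken before it, and the text does not secure the dates needed to tell them apart.

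It can also be said that meetings are already tracked to some degree, because staff must know whether one was held and whether it came after Day 7, and that a dated form item belongs in the full protocol. Table 1 and the booklets are not shown, so a timing note there cannot be ruled out. The visible text has none, and only a proportion of standard meetings is observed.

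Three stronger readings are tempting and are not supported:

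- **That a known share of control dyads is affected while the intervention site is clean.** Assuming that 30–60% of the 20 control dyads have a meeting, and that one third to one half of those meetings precede the family booklet, gives 20 × 0.30 × 1/3 = 2 to 20 × 0.60 × 1/2 = 6. Both rates are invented, and Day 7 is only a fallback. Setting the result against zero study meetings before baseline at the other site compares different kinds of meeting. Usual-care meetings before baseline at the intervention site are not shown to be zero.
- **That usual care as a whole would appear to change nothing.** Only the affected dyads lose the meeting's effect from their change.
- **That the study needs a before-and-after reading of standard meetings.** No objective asks for it. The measures are judged by completion, feedback and preferences.

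**Conclusion.** The point holds in limited form. A control pre-test can follow a family meeting without deviation, while the intervention pre-test must precede the planned one. That weakens the claim of equivalent pre- and post-tests and the secondary between-group comparison.

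The frequency cannot be computed for either site, and the effect per dyad is unknown. The loss arises only if a meeting has a lasting effect, and it matters only where change from baseline is read. Statistical methods plans between-group differences without defining a change score; a comparison of follow-up scores alone would not carry this error.

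The weight is modest, because this is an unpowered feasibility study with a qualitative primary outcome. It is still worth correcting before recruitment, since meeting dates that were never recorded may not be recoverable at analysis.

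**What to change.** 1. **Both sites:** record whether any family meeting has taken place this admission and on what date, so that each meeting can be placed relative to every baseline and repeat measure.
2. **Control site:** ask consented patients and relatives to complete their booklets before a scheduled standard meeting where possible, mirroring the intervention schedule. Only the booklet moves. When and whether a meeting is held stays with the facility.
3. **Analysis:** keep all dyads in the main usual-care comparison. Flag those with a meeting before baseline, and show the change summary with and without them. They should not simply be dropped: who gets an early meeting is a clinicians' decision, so removing them would select on it and shrink a group of 20.

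The cost is one dated item per booklet, one sentence in the control schedule, and slightly less uniform control baseline timing. Meetings held before consent, which is sought on Days 2–3, cannot be covered by the second step and can only be flagged.
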